## Abstract

**Background:**

The World Health Organization recommends universal iron supplementation for children aged 6–23 months in countries where anaemia is seen in over 40% of the population. Conventional ferrous salts have low efficacy due to low oral absorption in children with inflammation. Haem iron is more bioavailable, and its absorption may not be decreased by inflammation. This study aims to compare daily supplementation with haem iron versus ferrous sulphate on haemoglobin concentration and serum ferritin concentration after 12 weeks of supplementation.

**Methods:**

This will be a two-arm, randomised controlled trial. Gambian children aged 6–12 months with anaemia will be recruited within a predefined geographical area and recruited by trained field workers. Eligible participants will be individually randomised using a 1:1 ratio within permuted blocks to daily supplementation for 12 weeks with either 10.0 mg of elemental iron as haem or ferrous sulphate. Safety outcomes such as diarrhoea and infection-related adverse events will be assessed daily by the clinical team (see [name] et al. Additional file 4_Adverse event eCRF). Linear regression will be used to analyse continuous outcomes, with log transformation to normalise residuals as needed. Binary outcomes will be analysed by binomial regression or logistic regression, Primary analysis will be by modified intention-to-treat (i.e., those randomised and who ingested at least one supplement dose of iron), with multiple imputations to replace missing data. Effect estimates will be adjusted for baseline covariates (C-reactive protein, alpha-1-acid glycoprotein, haemoglobin, ferritin, soluble transferrin receptor).

**Discussion:**

This study will determine if therapeutic supplementation with haem iron is more efficacious than with conventional ferrous sulphate in enhancing haemoglobin and ferritin concentrations in anaemic children aged 6–12 months.

**Trial registration:**

Pan African Clinical Trial Registry PACTR202210523178727

**Supplementary Information:**

The online version contains supplementary material available at 10.1186/s13063-024-08101-0.

## Background {6a and 6B}

In sub-Saharan Africa, conventional iron supplementation using ferrous salts has limited effectiveness, primarily due to impaired non-heme iron absorption caused by infections and inflammation. Although haem iron has greater bioavailability, it has never been evaluated in children in an LMIC setting. In a before-after study without a control group among pregnant Kuwaiti women with gestational age 14–26 weeks with an initial haemoglobin concentration of 80–10 g/L, daily supplementation with haem iron tablets (Optifer®; 1 tablet twice/day) for ≥ 3 months resulted in notable increase in the mean haemoglobin concentration (from 84 to 112 g/L; *p* < 0.003) and mean ferritin concentrations (from 22.6 to 112.8 μg/L; *p* < 0.04). Only 1.7% (2/117) of the women studied developed gastrointestinal adverse effects, and no other side effects were recorded [1]. The present trial will compare the supplementation with 10 mg of haem iron versus ferrous salts in young Gambian children (ages 6–12 months) using a commercially available haem iron polypeptide (HIP) produced by hydrolysis of bovine haemoglobin.

Most iron supplementation trials, and all institutional programmes in Africa, use ferrous iron salts (typically sulphate or fumarate). These are cheap but have low efficacy, particularly in children living in rural Africa [2]. The very low efficacy of iron administration is a universal problem across all iron supplementation trials in low- and middle-income countries [2]. This is likely driven, at least in part, by hepcidin-mediated blockade of iron absorption secondary to infections and inflammation [3]. As an example, we have recently completed 2 trials in rural Gambia with 400 children aged 6–24 months [4] and 500 second trimester pregnant women [5]. Despite administering iron for 12 weeks (12 mg/day to children and 60 mg/day to pregnant women) with an additional 15 micronutrients and with all doses taken under direct supervision, we only achieved a 0.65 g/dL increase in haemoglobin concentration in the children and 0.33 g/dL in the mothers. The prevalence of anaemia dropped only from 91 to 77% and from 59 to 45%, respectively.

Haem iron is the most bioavailable form of iron and is readily available from meat, poultry, and some types of fish [6, 7]. Haem iron uptake through enterocytes is incompletely understood in children, but it is known to travel, at least in part, via an alternative absorption pathway to non-haem iron. This hypothesis is supported by the following evidence: (1) there was no evidence that hepcidin concentrations affected haem iron absorption in a study of pregnant (*n* = 18) and non-pregnant (*n* = 11) women [8], and (2) once inside enterocytes, haem induces the degradation of the transcriptional repressor Bach1 [9]. Bach1 regulates haemoxygenase-1, so that haem manages to ensure its own detoxification by increasing levels of HO-1, which liberates iron from haem. However, Bach1 also represses ferroportin [10]. Thus, haem uptake both facilitates the release of iron from the porphyrin ring within the enterocyte and its subsequent release from the enterocyte into the circulation via ferroportin. The strong upregulation of ferroportin at the transcriptional level, mediated by haem-induced Bach1 degradation, could potentially counteract the inhibition of ferroportin protein by hepcidin.

## Objectives {7}

The primary objective will be to determine if the efficacy of haem iron supplementation using a commercially available haem iron polypeptide (HIP) is superior compared to conventional ferrous sulphate.

## Methods/design {8}

### Study design

This will be a 2-arm parallel randomised controlled superiority trial, with participants, field staff outcome assessors and biostatisticians blinded to the treatment arm. The trial will be conducted in rural Gambia, and potential participants will be recruited from vaccination clinics or their communities. A total of 208 participants will be randomised to either haem iron or ferrous sulphate using a 1:1 allocation ratio and supplemented daily for 84 days (Fig. 2).

### Ethics and oversight {5d, 23, 24 and 25}

The study was approved by the Scientific Coordinating Committee of the Medical Research Council (MRC) Unit The Gambia and the Joint Gambia Government MRC Ethics Committee and the Ethics Committee at the London School of Hygiene and Tropical Medicine (LEO27648). Protocol amendments will be submitted through the same committees. This trial will be conducted according to the principles of Good Clinical Practice, with oversight from a Data Safety and Monitoring Board (DSMB). The Clinical Trials Department at the MRCG@LSHTM ([contact]) will audit the trial. The Clinical Trials Department will conduct a site initiation visit followed by regular visits. The first interim monitoring visit (IMV) will be done once signed informed consent is obtained from at least 50 participants. Thereafter, a visit will be done monthly. The frequency of the interim visits may be scaled down or increased if required at the discretion of the sponsor.

#### Composition of the data monitoring board, its role and reporting structure {21a}

An independent data safety management board (DSMB) was constituted before the start of the study to provide oversight. It is comprised of four members including two area experts, one clinical research specialist and one trial statistician. The DSMB will be responsible for reviewing safety data and data related to recruitment and retention. The role of the DSMB will be to advise the sponsor and trial management group if, in their view:There is a level of concern about the safety of participants in any treatment arm such that future recruitment to that arm is no longer judged to be appropriate.The quality of the safety data generated is of such concern (in terms of completeness and accuracy) that an assessment of the participants’ safety is not considered to be possible.The quality of the safety and other data generated is of such significant concern (in terms of completeness or accuracy) that the results of the trial are likely to be called into question irrespective of the outcome.The rate of recruitment is such that it is unlikely that the trial will be completed successfully.They become aware of other data addressing the same or related questions to those in the IDeA3 study such that the trial is no longer considered to be justified in its current form.

The charter of the DSMB is kept in the Trial Master File and is available on request.

#### Trial sponsor {5b and c}

The trial sponsor is the Medical Research Council Unit The Gambia at London School of Hygiene & Tropical Medicine, [name]. Neither the funders nor the sponsor will be involved in the conduct of the study.

#### Confidentiality {27}

To safeguard the confidentiality of participants, all identifiable data collected by the study team will be securely stored and protected in accordance with the Data Protection Act. If there is a need to share data about participants through a public data repository or directly with other researchers, precautions will be implemented to ensure that participant information remains unidentifiable. All data sharing will adhere to the guidelines outlined in the UK/European General Data Protection Regulation (GDPR).

### Participant retention {18b} and post-trial care {30}

Participants will be able to withdraw from the study at any time without providing a reason for their withdrawal. However, if participants provide a reason, this will be documented with the date of participant discontinuation. If an adverse event is associated with the participant’s discontinuation, it will be described, even if it is not the primary reason for withdrawal.

All participants will be passively monitored by the clinical team during the study and 2 weeks post-supplementation for any adverse (AE) or serious adverse events (SAE).

### Recruitment and screening {9, 11c, 15 and 18b}

Before the study begins, meetings with local elders and community leaders and group meetings with community members in the villages within the recruitment area (see Additional file 1: Table S1: list of villages that will be included) will be conducted to inform and educate the general public and potential participants about the study. To ensure effective communication and integration in the communities, field workers will be assigned to participants based on their language fluency (e.g. Mandika, Fula, Wolof). Potential participants will be identified in vaccination clinics or in their homes by trained field workers who will explain the study to the parents or guardians individually.

### Who will take informed consent? {26a, b}

The discussions about the trial and informed consent will take place in a private location chosen by the participants. For illiterate participants, an impartial witness will be present. Before participants provide informed consent, the field staff will assess their understanding using an electronic case report form (eCRF). If participants fail the assessment, the study information will be explained to them again. If participants fail the assessment for a third time, consent will not be obtained, and this will be documented as consent failure in the relevant eCRFs. Participants who refuse to provide consent or fail the screening will not be enrolled in the study, and this will be recorded in the relevant eCRFs. Anaemic participants will be invited for a baseline screening and eligible individuals enrolled in the study. Note that the informed consent document contains the following sentence: “I agree to further research on my child’s samples including genetic testing.”

The follow-up period will be 84 days (12 weeks) with 2 weeks of post-study follow-up for adverse events (Fig. 1). Figure 1 shows a schematic of the study design {13}. Table 1 shows the sequence of events in the trial from the perspective of the study participants (Table 1).

**Fig. 1 Fig1:**
[figure not shown]
Schematic of the study design

**Table 1 Tab1:** Sequence of events

Study activities	Prior to enrolment	Intervention period												Follow-up	
	Week (Wk) 0	Wk 1	Wk 2	Wk 3	Wk 4	Wk 5	Wk 6	Wk 7	Wk 8	Wk 9	Wk 10	Wk 11	Wk 12	Wk 13	Wk 14
**Informed consent**	x														
**Pre-screening for anaemia/eligibility**	x														
**Demographic data collection**		x													
**Anthropometry measurement**		x											x		
**Screening for inclusion and exclusion**		x													
**Baseline sample collection**		x													
**Randomisation**		x													
**Daily supplementation**		x	x	x	x	x	x	x	x	x	x	x	x		
**Weekly feeding questionnaire**		x	x	x	x	x	x	x	x	x	x	x	x		
**Monitoring of adverse events**		x	x	x	x	x	x	x	x	x	x	x	x		
**Endline sample collection**													x		
**Post supplementation follow-up**														x	x

### Eligibility criteria {10}

Once consent is provided by parents/guardians, participants will be screened for anaemia (Hb < 11.0 g/dL) using HaemoCue 301 (HemoCue®, Ängelholm, Sweden). Participants who are anaemic will be invited to the study sites for further eligibility screening through the assessment of the inclusion and exclusion criteria by study nurses or research clinicians. We will include children between the ages of 6 to 12 months of age who are anaemic (Hb 7– <11.0 g/dL). Any children who are acute or chronically ill, have Hb < 7.0 g/dL, have fever (axillary temperature > 37.5 °C), history of low birth weight (< 1500 g), prematurity (born gestational age < 34 weeks), are planning to use of vitamin supplements or have any condition that in the opinion of the investigator or clinical team might compromise the safety or well-being of the participant or compromise adherence to protocol procedures will be excluded. Children who are found to be unwell during the screening process will be referred for care to a local clinic.

### Randomisation and blinding to allocation and treatment {16a, b and c and 17a}

Prior to baseline sample collection, a list of participant IDs will be generated. The participant ID will be comprised of a four-letter study code (IDEA), a four-digit unique number (e.g. 0001–3000) and a check letter (e.g. A–Z). Once participant eligibility is confirmed, the sub-investigator or data manager will assign each participant a unique intervention code (i.e. 1–6) by running the electronic randomisation CRF in RedCap. The password-protected randomisation eCRF will be developed and will only be accessible by the data manager. In order to blind the treatments, there will be six intervention codes (1–6) of which three will be assigned to the ferrous sulphate arm and the other three to the haem iron arm by the pharmacist (see the section describing IP below). The treatment randomisation code will be kept in a locked box, only accessed if unblinding becomes necessary. The study IDs with their respective treatment codes will be exported from RedCap as a PDF and sent to the clinical team who will issue the assigned treatment to the field team daily. To maintain the integrity of blinding, the randomisation code will be stored in a sealed, time-stamped envelope. This envelope will be securely kept in a locked box and will only be accessed if unblinding becomes necessary. The data collectors, participants, investigators and biostatisticians will be blinded to the intervention.

### Intervention {11a}

The haem iron will be purchased commercially packaged as a black powder in clear capsules (Proferrin, Colorado Biolabs, USA). Ferrous sulphate iron will be purchased commercially as a black powder in a green capsule (Active Iron, Solvotrin, Ireland). A pharmacist will repackage both investigational products into identical clear capsules containing 10 mg of each product to ensure blinding. The intervention products will be divided into six intervention arms, labelled as arms 1 to 6. The pharmacist will label the bags containing the capsules with the investigational products (IP) based on the randomisation codes. As described above, the study team and participants will be blinded to the type of intervention given.

The intervention products will be stored at the field office, where the temperature will be monitored daily. The field staff will transport all intervention products to participants’ homes daily for 84 days. They will open the capsules and mix the powder with water in a teaspoon with the assistance of the parent/guardian to administer it to the children. If a participant vomits or spits out the intervention, a second dose will be re-administered and this information will be recorded.

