### Statistical plan

#### Sample size determination {14}

The sample size was determined by the primary endpoints, haemoglobin concentration and serum ferritin concentration, which will both be measured 84 days after randomisation (Fig. 2) using Microsoft Excel™ with a 5% dropout rate; a total of 208 children will be randomised, which will be sufficient to (a) provide 90% probability that, if the real group difference in haemoglobin concentration is 5.0 g/L or more, the 95% CI for the difference would exclude 0 [calculation based on the assumption that the SD for haemoglobin is 10g/L for each group (estimate based on previous experience in many previous trials in African children)] and (b) have 90% probability that, if the real change of the geometric mean serum ferritin concentration in the haem group iron relative to the control group is 75% or more, the 95% CI for the ratio would exclude 0 [calculation based on the additional assumption that the variance of log_e_-(serum ferritin concentration, μg/L) equals 1.232 for each group [15]].

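### The basis of the 10 mg dose is stated inconsistently: elemental iron in the abstract, haem iron in the Background, product in the Intervention section

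*Protocol article*

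**What the plan says.** The article states the dose in three places, each on a different basis.

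- **Abstract, Methods:** "daily supplementation for 12 weeks with either 10.0 mg of elemental iron as haem or ferrous sulphate". The basis is elemental iron, and one figure covers both arms. The word elemental appears nowhere else in the article.
- **Background {6a and 6B}:** "The present trial will compare the supplementation with 10 mg of haem iron versus ferrous salts". The figure is attached to haem iron. No separate figure is given for the ferrous arm, and the basis is not named. The same sentence describes the haem product as a "commercially available haem iron polypeptide (HIP) produced by hydrolysis of bovine haemoglobin".
- **Intervention {11a}:** both commercial powders are to be repackaged, and the pharmacist will "repackage both investigational products into identical clear capsules containing 10 mg of each product to ensure blinding". The basis is the product, and the section states no quantity of iron.

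The article does not give the iron content per milligram of either product, the fill weight or the number of capsules per daily dose. Nor does it say that 10 mg of product is shorthand for 10 mg of iron. Such details may properly sit in the full protocol. The point here is that the three statements present in the article do not agree.

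**The concern.** The primary objective is superiority of haem iron over ferrous sulphate. The Discussion goes further and treats the result as possible support for absorption pathways that inflammation does not affect. Both inferences need the arms to differ in the form of iron and not in its amount.

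The Intervention section defines the treatment contrast, yet it is the one place where the quantity is expressed as product. If that sentence were followed as written, form and amount would vary together. Any difference in day-84 haemoglobin or ferritin, or the lack of one, could then not be assigned to form. Randomisation and baseline adjustment would not help, because the imbalance would be part of the assigned treatment and not a chance difference between children. A larger sample would not help either.

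**Working it through.** **Inputs from the article.** Stated dose: 10.0 mg of elemental iron in each arm (abstract). Stated capsule content: 10 mg of each product (Intervention). Haem product: a polypeptide from bovine haemoglobin (Background). Ferrous product: ferrous sulphate (Intervention).

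**Step 1: can the stated dose be reproduced from the stated capsule content?** Let f be the fraction of a product's mass that is iron.

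- Iron per capsule = product mass × f.
- Setting 10.0 = 10 × f gives f = 1.

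That is pure iron. A haem polypeptide and a ferrous salt both have f below 1, so the stated dose is not reproduced in either arm if product means powder mass. This step needs no outside figure.

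**Step 2: would the arms at least be equal?** With the same product mass in each arm, the ratio of iron (ferrous to haem) is f(ferrous) / f(haem). It equals 1 only if the two fractions coincide. Giving the same number of capsules per day in both arms multiplies both amounts alike and leaves the ratio unchanged.

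**Step 3: illustration of size.** The article gives no fractions. The assumption here is pure compounds, with fractions from molar masses (iron 55.845 g/mol).

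| Compound assumed | Iron fraction | Iron in 10 mg |
|---|---|---|
| Ferrous sulphate, heptahydrate | 55.845 / 278.01 = 0.201 | 2.0 mg |
| Ferrous sulphate, anhydrous | 55.845 / 151.91 = 0.368 | 3.7 mg |
| Haem | 55.845 / 616.49 = 0.0906 | 0.9 mg |

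The ratio runs from 2.01 / 0.906 = 2.2 to 3.68 / 0.906 = 4.1.

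The haem figure is an upper limit, because the polypeptide carrier adds mass without iron. If the preparation were 1% to 5% iron, 10 mg would hold 0.1 to 0.5 mg. Excipients in the commercial ferrous product would lower its figure too. The range of 2.2 to 4.1 therefore describes pure compounds and not the purchased capsules.

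**Step 4: the opposite reading.** If 10 mg means iron, the powder needed under the same assumption is 10 / 0.0906 = 110 mg or more for haem, against 10 / 0.368 = 27 mg to 10 / 0.201 = 50 mg for ferrous sulphate. The abstract's dose then holds in both arms, but the powder masses differ unless a filler is used, and the article mentions none. Because field staff open the capsules before giving the dose, the basis chosen also has some bearing on how alike the contents look.

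**The case against.** The strongest reply is that this is one loose noun. The Intervention section never says mass or fill weight. The sentences just before name the products as kinds of iron: "The haem iron will be purchased commercially packaged as a black powder in clear capsules" and "Ferrous sulphate iron will be purchased commercially as a black powder in a green capsule". On that reading, 10 mg of each product means 10 mg of each iron, which agrees with the abstract and with the Background's figure for haem iron. The number 10 is the same throughout. The context also fits. The Background reports that 12 mg of iron a day produced only a modest haemoglobin rise in Gambian children, and a trial seeking better efficacy is unlikely to have planned 0.9 mg. Full protocol versions exist and may state the fill exactly.

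Most of this stands, and it limits the point in four ways.

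- A reader might infer that the children received unequal iron. The article does not show that. No place in it assigns different iron doses to the arms.
- A reader might say the statements can never be reconciled. They can be, if product is read as iron from each product. They conflict only when product is read as powder mass.
- A reader might take the phrase to mean both products in one capsule. The abstract, the study design, the randomisation section and the division into labelled arms all exclude this.
- A reader might assume the capsules were filled from this section. The article does not say what instructions the pharmacist used.

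The reply does not remove the inconsistency. The only explicit elemental-iron statement is in the abstract, the Background gives no clear figure for the ferrous arm, and the section that defines the intervention uses a different basis. That section gives blinding as its purpose, which could fit equal fills, so the literal reading is unlikely but not fanciful.

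**Conclusion.** The concern holds as an inconsistency in the stated basis of the dose, in a section on which the iron-form comparison depends. Taken literally, the Intervention wording cannot give 10 mg of elemental iron in either arm, and it would give the arms unequal iron unless the two products' iron fractions happened to match. That conclusion rests only on neither product being pure iron.

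The size is illustrative: 2.0 to 3.7 mg against at most 0.9 mg, a ratio of 2.2 to 4.1, assuming pure compounds. It measures the literal reading only and does not estimate what was given. Under that illustration the haem arm would have less iron. A null result could then not separate the absence of an absorption advantage from a smaller amount of iron. For the commercial formulations, the article does not fix even the direction of any difference.

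Loose wording for 10 mg of iron from each product is the likeliest explanation. It should still be settled before analysis and reporting, because an equal-iron comparison is what gives the primary result its meaning.

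**What to change.** Reconcile the abstract, the Background and the Intervention section so that each arm's quantity is stated on one basis, either elemental iron or product mass, in the same words in all three places. Confirm from the repackaging records what was filled for each product, and do this before the arms are described as iron-equal. If the records show unequal iron, the report should say so, and the comparison should be described as one of products and not of iron forms. This review does not say which figure is right.

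The cost is a wording correction and a check of existing pharmacy records. The design, sample size and data collection are unaffected, and the check remains possible after enrolment has ended.
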